###### Psychosocial

*Structured interview.* Mental health will be assessed in this study using the new computer-assisted National Comorbidity Survey-Replication Composite International Diagnostic Interview (the NCS-R-CIDI), which arose out of a joint project of the World Health Organization and the former US ADAMHA. The reliability and validity of the original paper-pencil CIDI was demonstrated in both large epidemiological studies as well as in smaller validity studies.266-269 The NCS-R-CIDI is now being used by three International Consortia as part of the World Mental Health 2000 Initiative,270,271 which seeks to characterize mental health in 27 countries (see Girolamo & Bassi272). The newer CIDI has been adapted for computer-assisted administration (versus the CIDI-Auto which is self-administered). It generates mental health diagnoses using DSM-IV criteria. The reliability and validity of the CIDI is supported by the extensive field testing of the instrument,272 the prior validation of the paper-pencil CIDI, its reliance on ICD-10 and DSM-IV criteria and earlier validation studies.273

The NCS-R-CIDI has notable strengths that make it appropriate for the present research. First, it permits assessment and diagnosis over three timeframes (lifetime, past year, and past month). In the present work we will administer the lifetime NCS-R-CIDI in Project 1: (Efficacy) and the past-year versions in the current project (Year 1, 2 & 3 follow-ups). In addition, it also assesses such relevant constructs as quality of life (daily functioning, social and family relationships), impact of mental health symptoms, and constructs relevant to physical illness (major diseases, use of clinicians). Also, it permits skip patterns so that individuals may be briefly screened for a disorder/condition, and it is suitable for administration by trained lay interviewers. NCS-trained staff will train lay interviews in all structured interview measures. Interviewers will be subject to repeated reliability assessments throughout the study.

We plan to administer the following NCS-R-CIDI components: mental health (Depression, Irritable Depression, Panic Disorder, Specific Phobia, Social Phobia, Agoraphobia, Generalized Anxiety Disorder, Suicidality, Alcohol Use, Tobacco Use, Neurasthenia, Obsessive-Compulsive Disorder, Worries and Unhappiness, and 30-Day Symptoms), physical health and health quality of life (Use of Services, 30-Day Functioning, Chronic Conditions). Importantly, we are deleting a number of CIDI scales in the interest of reducing burden (e.g., all childhood disorder scales, eating disorders, gambling, demographics).

These scales will provide critical information on diagnosis and dimensional information on mental health, physical health, their impact on quality of life, and health & mental health care utilization. These NCS-R-CIDI measures will be supplemented with other measures to achieve a greater sense of status in critical domains.

*Psychometric status of additional instruments.* The instruments used in this study (see Table 4) all have psychometric properties that support the inferences for which they are being used. For instance, the MPQ brief form (MPQ-BF) has excellent psychometric properties as a personality measure.147 The Wisconsin Dependence Measure (WISDM-68) the Wisconsin-Probability of Relapse and Smoking Measure (WI-PRISM), and the Fagerström Test of Nicotine Dependence (FTND) have been shown to predict dependence outcomes such as relapse and withdrawal severity.138,156 In fact, there is a substantial literature attesting to the positive psychometric properties of all of the measures that will be used: e.g., the PANAS,274 the Quality of Life Inventory,275 the Depression Proneness Inventory (DPI),154,276 and so on. The psychometric properties of other, chief measures were discussed earlier.

Genotyping

DNA sequencing will take place at the University of Utah Huntsman Cancer Institute. It has four ABI 3700’s and one ABI3730 which can run a total of 28,000 sequence ladders per week. SNP typing will be performed by the ABI SNPlex system. This system can detect 4500 SNPs in parallel in as little as 15 minutes. Extensive capabilities also exist in this center for bioinformatics that enable investigators to collect and analyze DNA sequence, haplotype and SNP data. DNA extraction is described in Project 1.

Compensation

Participants will be compensated for completion of vital study milestones. Specifically, we will compensate participants $100 for completing each of the three annual in-person study visits to take place at Months 12, 24, and 36 (total compensation $300). In addition, we will send participants birthday cards each year thanking them for their participation, and small gifts labeled with study identifiers and phone/email information (e.g., pens, refrigerator magnets, notebooks) (see “Steps to reduce attrition” above).

**Analytic Plan**

*Representing Constructs: Selection and Synthesis of Measures*. One virtue of this research is that many of the important constructs are assessed with multiple measures. The measures are not only psychometrically strong individually, but their conjoint use permits us to determine convergent validity. Moreover, some of these measures are collected in very different ways and this has the advantage of reducing method variance. While use of multiple measures confers advantages, it also requires decisions regarding which measures are to be used for which purposes.

The general approach we will adopt with dependent variables is as follows: when there are multiple measures of a type of dependent variable, we will examine the interrelations among the measures, determine the stability of findings across the class, and perhaps analyze a composite measure. For instance, with respect to *mental health* the NCS-R-CIDI yields categorical diagnoses and symptom counts. In addition it comprises measures of mental health quality of life, impact of mental health symptoms on daily functioning, and use of psychiatric services. We will explore how these different indicators are interrelated, and whether predictors bear similar relation to the different indicators. The latter will help us determine whether a finding is robust and stable. This strategy requires that we report findings across the different measures of common constructs. Finally, we may examine composite measures. For instance, in some analyses we plan to collapse across all major anxiety, affective, and substance use diagnoses (taking into account comorbidity). We plan to employ a similar strategy across the different major types of dependent variables that have multiple indicators: e.g., atherosclerosis, quality of life, nicotine dependence, alcohol use/abuse. For instance, alcohol variables will arise from time-line follow-back data, the Short Inventory of Problems, CIDI Diagnosis, and electronic diary data gathered in Project 1. Smoking relapse and calendar measures of smoking over each year will be produced using data generated by the time-line follow-back procedures used in follow-up interviews. This will produce measures of continuous abstinence, point-prevalence, and percent days smoking each year. Amount of smoking will be determined in each 7-day point prevalence period. Any of these could be used in analyses, but for modeling over time, percent days smoking over each year combined with heaviness measures should yield the most useful measures of tobacco exposure over time. Use of other tobacco or nicotine containing products will also be examined.

With respect to independent variables, we will use model-building procedures (described below) to systematically select best measures from a class, and also report prediction stability across measures.

*Data Acquisition and Preparation.*Data will be inspected on a continuous basis over the course of the study to ensure that data acquisition is satisfactory. Virtually all of the data will be captured via computer entry, scannable forms and palm-top computers. One further data source will be data obtained from medical tests. These typically do not generate computer data files and when they do not, they will be double-entered.

*Data Comparisons.*This study will permit us to address numerous important questions about how quitting smoking and relapse are related to health and psychosocial outcomes, and for whom particular outcomes are especially likely. We cannot outline all of the analyses permitted by this data set. However, we will present analytic plans for several important outcomes. These will reveal the strategies that we will use and the relations to be tested.

We will identify a critical question, use regression methods to identify significant predictors of ultimate endpoints, and then use structural models to explore more complex relations among significant predictors across time. We will assess genetic correlates of critical phenotypes (e.g., nicotine dependence, quitting success, mental health status, and atherosclerosis status and progression) in a parallel research track. We will eventually combine genetic and nongenetic variables in integrated prediction models to determine potential mediators of genetic relations (e.g., via personality) and whether candidate genes predict particular endophenotypes (e.g., smokers reporting escalating or prolonged withdrawal124,125). Construction of genetic models will follow the principles outlined below.

*Predicting Discrete Endpoints.*Many clinicians and others interested in public health will primarily be interested in best-fitting models that predict outcomes (e.g., psychiatric diagnostic outcomes such as depression, or diagnoses such as diabetes, quality of life) at some future point in time. To address the prediction of outcomes at discrete points in time, we will use logistic and multiple regression models (for categorical & continuous dependent variables, respectively) in which ultimate status at Year 2 or 3 is predicted by both prequit and postquit variables.

In testing predictive relations we will follow a general strategy consistent with the model building recommendations made by Hosmer & Lemeshow.277

- We will identify on an a priori, substantive basis, the major predictors to be tested, control variables, and critical interactions. Predictors will include both static and dynamic variables gathered both before and after the quit attempt.
- We will then examine distributions and use transformations where appropriate.
- Missingness will be addressed through direct Maximum Likelihood estimation278 assuming that ignorability assumptions are appropriate and standard error and test statistics are robust.279
- We will test univariate relations for all substantive variables so that their nonresidualized relations may be reported. Univariate variables will be modeled in various ways discussed in the section “Representing Constructs”) in order to determine the generalizability of obtained relations.
- We will use model-building procedures described below to identify best-fitting models using all promising candidate measures identified in univariate analyses.
- We will engage in *secondary analyses* to explore the relations of other variables with important targeted outcomes. These analyses will explore models that are less clinically or theoretically important than those tested in primary analyses, but ones that may provide the basis for future hypotheses and research. If reported, secondary analyses will clearly be labeled as exploratory.

All logistic regression models will be developed and tested using procedures and recommendations of Hosmer & Lemeshow.277 For instance, variable selection will start with a careful univariate analysis of each variable, and computation of smoothed scatterplots for continuous variables. After univariate analyses, all independent variables with P-values <0.25 will be candidates for multivariate analyses. Subsequent variable selection will occur in the context of forward selection with a test for backwards elimination. Subsequent to the identification of a multivariate logistic model, the performance of each variable will be evaluated via inspection of the Wald statistic, and the comparison of the multivariate and univariate errors and regression coefficients. If a new model is generated this will be compared with the larger former model via the likelihood ratio test. Eliminated variables will be re-entered to ensure that they have not become valid predictors through the exclusion of other variables. The performance of all continuous variables will be tested for linearity of the logit and any hypothesized (*a priori*) interactions tested. Model fit will be assessed via the Hosmer-Lemeshow test and via area under the ROC curve. Standard model diagnostics will be used (e.g., inspection of leverage values, variance of residuals for covariate patterns). Construction of multiple regression models will be similarly standardized and subjected to appropriate diagnostics.280

Model building will follow strategies frequently used in longitudinal research.1 Thus, *control variables* will be routinely entered (e.g., gender, age, site, ethnicity, Project 1 treatment, SES). Change will be modeled via entry of pretreatment (baseline) measures of the dependent variable and via change scores (which protect against interpretive biases of partialled scores.281,282 Next, relevant *individual differences* will be entered: e.g., nicotine dependence, personality, and genotypes, depending upon the analysis. Then other *modifiable risk factors* will be entered: i.e., measures of diet, alcohol use/abuse, weight/BMI/waist circumference, stressors/distress, exercise, blood pressure, serum lipids, and exposure to second hand smoke. Principal relations will be presented both in univariate and multivariate models. Two-way interactions to be tested will be based upon a priori hypotheses for each tested model.

*Principal Hypotheses*

Hypothesis 1: Smoking cessation (amount of abstinence over the follow-up period coded either dichotomously or continuously) will be associated with *reversal or arrest of atherosclerosis* as assessed via CIMT. Baseline CIMT scores will be used to determine change. *Individual differences and control variables*: Progression will be greater among males283,284 and among those high in trait (MPQ) Negative Emotionality.2,4,8 The following *modifiable risk factors* will predict greater atherosclerotic progression: weight gain, fat intake,1 BMI, second-hand smoke, sedentariness, and high levels of stress (e.g., 5-7). Exercise/activity, however, will predict greater regression. Two critical interactions with smoking will involve second-hand smoke and gender since research suggests different impacts of smoking depending upon these variables.1,283

Hypothesis 2. Smoking cessation/reduction will be associated with positive changes in *mental health functioning* (from baseline status). Change will be measured from either baseline (lifetime) history of diagnosis, or baseline symptom levels, depending upon the analysis. While cessation may initially increase depression/depressive symptoms, long-term cessation will be associated with improved mental health status as reflected by lower rates of psychiatric diagnoses and reduced symptoms (thus, some analyses will focus on Year 2 and 3 symptoms/diagnoses). *Individual differences and control variables*: post-cessation symptoms will be positively related to trait (MPQ) Negative Emotionality and female gender (especially if diagnoses are restricted to internalizing disorders) and severity of prequit nicotine dependence. *Modifiable risk factors*: mental health symptoms/diagnoses will be inversely related to post-quit social support and physical health, and positively related to post-quit stressor occurrence and frequency of postquit heavy drinking days (relevant to dependent variables that do not themselves comprise alcohol diagnoses). No interactions are predicted for this family of analyses.

Hypothesis 3. Smoking cessation/reduction will lead to improved *quality of life*. We expect continuing smokers to report diminishing QOL levels over the follow-up period (relative to baseline), and we expect exsmokers to report improving QOL. Change will be measured from baseline levels of tested measures (e.g., Quality of Life Questionnaire or other QOL indicator: e.g., 30 day functioning). *Individual differences and control variables*: Improvement in QOL will be inversely related to age.  *Modifiable risk factors:* QOL improvements will be inversely related to postquit heavy drinking days, postquit increase in BMI, post-quit measures of physical health symptoms (CIDI Chronic Conditions & 30 Day Symptoms) and positively related to postquit social support available in the social network. We make a further prediction that much of the improvement in QOL will be mediated by postquit psychiatric symptoms/disorders. We predict that the influence of smoking on QOL will be moderated by postquit weight gain/BMI as those gaining more weight will show a reduced relation between cessation and QOL improvements.11

Hypothesis 4.Smoking relapse late in the follow-up period (>1 yr postquit) will be related to presence of alcohol use in the person’s social network/dyad and to presence of smokers in the social network/dyad and alcohol use. Late relapse will be modeled both as 3-year point-prevalence or latency from 1-year post-quit. *Individual differences and control variables*: Importantly, baseline nicotine dependence will *not* predict late relapse, nor will female gender (although this may be because these factors may have already exerted their influence in the first year of follow-up which we will examine). *Modifiable risk factors:* We expect late relapse likelihood will be positively related to both number of drinking days and heavy drinking days (both postquit), to number of smokers in the social network and contact with such smokers (postquit), and to spousal smoking among partnered participants.

Hypothesis 5. Abstinence from smoking will be associated with reductions in the frequency of drinking-days in the post-quit period. Change will be determined from prequit frequency of drinking. *Individual differences and control variables*: Postquit drinking frequency will be positively related to male gender, and inversely related to MPQ Constraint and SES. *Modifiable risk factors:* Postquit drinking frequency will be inversely related to presence of drinking and smoking in the social network, and inversely related to exercise level. Finally, we expect an interaction between prequit diagnosis of alcohol abuse or alcohol problems (SIP) and smoking status. We believe these variables will reduce the impact of smoking cessation on drinking. Thus, smoking cessation will affect drinking frequency principally among those with fewer drinkers in their social network and who show no prequit drinking problems. These analyses will not reveal the temporal ordering of drinking and smoking influences, or their reciprocal effects over time. These issues will be addressed in structural models described below.

Secondary analyses. These will examine the predictors of the following postquit outcomes: (1) *physiological outcomes other than CIMT*: BART endothelial function, lipid measures, blood pressure, diabetes indicators, (2) *diet/nutrition/weight*: BMI, waist circumference, diet measures, (3) *physical fitness/activity*: pedometry, treadmill, IPAQ (4) *health-related quality of life*: NCS-R-CIDI physical symptoms & functioning, (5) *quality/nature of the social network*: size, smoking and alcohol use in network, supportiveness of network. It is important to note that the above models will be carefully refined with on-going consultation with our expert Co-Investigators in relevant fields.

*Structural Models.* We will use structural modeling to take advantage of the truly prospective, multiple measurement properties of the design. In particular we will use latent trajectory models (LTMs) to examine direct, indirect, and reciprocal relations among critical variables (including latent variables) over time. In these models intercepts and trajectories of repeated measures (e.g., smoking over time) will be modeled as random variables. In constructing trajectory models linear and quadratic trajectories will be modeled, as well as completely latent change functions since different inter-measure intervals may increase the value of shrinking or stretching time to capture trajectories.285,286 Analyses will be developed programmatically such that more complex structures will be tested only after characterization of simpler (nested) models. For instance, in modeling change in smoking or alcohol intake over time, we will first determine functional forms of these dynamic variables, then determine how they are influenced by key individual-difference exogenous variables (e.g., baseline nicotine dependence, history of psychiatric disorder), and then determine whether obtained relations are affected by inclusion of control variables (gender, site, ethnicity). Fit will be determined via conventional fit statistics.287

LTM methods allow for modeling of both mediational and moderating effects. In the former one can determine factors that mediate the effects of variables on the intercepts or trajectories of targeted variables (e.g., mental health outcomes). In the latter, one can determine *under what conditions* a relation exists between a predictor and a targeted construct. Moreover, we will use an autoregressive LTM to characterize the performance of two different variables measured repeatedly and their interdependencies over time.286 This will reveal, for example, whether time-specific values in drinking, relative to average drinking values, predict subsequent values in smoking (relative to average levels of smoking), and vice versa. There will be six repeated measures for follow-up phone variables and four measures for those gathered at in-person visits. (LTM will not be used for variables gathered only twice: e.g., Carotid IMT). Latent variables may be used for some central constructs (e.g., mental health status).

Figure 5 depicts an example of a multivariate unconditional latent trajectory model (LTM) for exploring alcohol use and smoking (modeled with only 4 repeated measures). Such models might also be used to explore relations between smoking and psychiatric symptoms, and between smoking and weight gain. Control variables such as those described in the “Predicting Discrete Endpoints” will be used as exogenous variables (MPQ Constraint, Gender, and Smoking in the Social Network). One exemplar set of predictions (Figure 5) would be that Gender will influence both initial drinking and smoking indices (Intercepts) with males showing higher levels. Low levels of trait Constraint would predict high initial smoking and drinking, and predict high levels of smoking over time. Post-quit smoking in the Social Network would also predict a reduced decline in smoking over time. Smoking and drinking might be inter-related in that higher smoking intercepts predict reduced declines in drinking over time.

Power

After accounting for relapse and attrition (initial N=900), we expect that data for at least 300 continuously abstinent and 450 smoking participants to be available for analysis. These estimates are based on the expectation that approximately 9% of the participants enrolled in Project 2 will either relapse (approximately 4% per year) or drop out of the study (approximately 5% per year) in years 2 and 3. The large number of primary and secondary hypotheses precludes presentation of power estimates for all possible comparisons. Two power analyses are presented below of central, discrete endpoint hypotheses.

*Long-term smoking status and atherosclerotic progression:* The best relevant estimates of CIMT effect sizes were reported by Howard et al.1 These authors analyzed CIMT change over a 3-year period in terms of smoking status (current, past, never) and ETS exposure. Howard et al.1 used mean common CIMT as the measure of progression (CIMTmean ). The authors computed linear regression models that controlled for demographic, life-style, and other risk factors and found a significant difference between current and past smokers of 7.3 m, equivalent to a 20% difference in progression.

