These goals are part of a research program that has three overarching aims: (1) To provide a broader, more complete view of the long-term effects of quitting and quitting failure than has been available thus far; (2) To reveal the extent to which other modifiable risk factors such as drinking, weight gain, diet and exercise contribute to observed outcomes; and (3) To identify which smokers are most likely to develop positive and negative outcomes. Such information should prompt greater quit rates and ensure that each smoker enjoys the full benefits of quitting. In addition, this research will identify individual difference variables (e.g., genotypes) and other modifiable risk factors that predict important physical health, mental health, smoking, and drinking outcomes. This information should be of great benefit in devising preventive interventions.

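### Logistic models chosen by P<0.25 screening and stepwise selection are assessed by an AUC with no internal validation named, so the AUC will be optimistic, most of all for binary late relapse

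*Protocol*

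**What the plan says.** The rule is in the protocol's Analytic Plan, under *Predicting Discrete Endpoints*, and its scope is general: "All logistic regression models will be developed and tested using procedures and recommendations of Hosmer & Lemeshow".

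- **Screen:** "all independent variables with P-values <0.25 will be candidates for multivariate analyses".
- **Selection:** "Subsequent variable selection will occur in the context of forward selection with a test for backwards elimination". Dropped variables are then tried again.
- **Assessment:** "Model fit will be assessed via the Hosmer-Lemeshow test and via area under the ROC curve".
- **Candidate pool:** the same section intends to "identify best-fitting models using all promising candidate measures identified in univariate analyses". Under *Representing Constructs*, model building is also used "to systematically select best measures from a class, and also report prediction stability across measures".
- **Purpose:** the general strategy is to "use regression methods to identify significant predictors of ultimate endpoints". The third overarching aim in Specific Aims is "To identify which smokers are most likely to develop positive and negative outcomes".

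Some safeguards exist. Major predictors and interactions are to be named beforehand, control variables are entered routinely, and secondary analyses, if reported, are labelled exploratory. The protocol gives no number of candidates, no P-to-enter or P-to-remove, and no validation step.

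**The concern.** An AUC computed on the participants who were used to choose the variables measures how well the model fits those participants. Part of it comes from having searched. With many candidates and few events, that part can be large even when nothing predicts the outcome.

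The safeguards do not remove this part. Naming major predictors beforehand does not stop the screen and selection that follow in the same list. Agreement across related measures of one construct in the same people is weak reassurance, because those measures can share one chance association. A Hosmer-Lemeshow test on the fitting data checks calibration in those data only.

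At stake is the use of these models to say who is at risk. Discrimination would be overstated, and some of the predictors named would not replicate. Late relapse is the most exposed, because it combines few events with a wide range of possible predictors.

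**Working it through.** **1. The protocol's own figures.** These reproduce.
- Retained continuous abstainers: 360 × 0.91² = 298 (stated 300). Smokers: 540 × 0.91² = 447 (stated 450). Total retained: 900 × 0.95² = 812 (stated 812).
- Power for 21% v 30% with 300 and 450 participants, two-sided .05: 0.789 (stated .79).
- No figure is given for the selection procedure itself, so there is none to reproduce.

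**2. Events available.**
- Late relapse uses 360 abstainers at 12 months (*Enrollment*), 4% relapse a year (*Smoking outcomes*) and 5% attrition a year (*Attrition*). Year 2 gives 360 × .04 = 14.4. Year 3 gives 360 × .91 × .04 = 13.1. The total is **27.5**, with 360 × .95² = 325 retained.
- Over the protocol's 3-5% relapse range: 360 × .03 + 360 × .92 × .03 = 20.7, up to 360 × .05 + 360 × .90 × .05 = 34.2.
- The routine control variables listed are gender, age, site, ethnicity, Project 1 treatment and SES, which is at least six terms. 27.5 / 6 = 4.6 events per term before any candidate enters.
- Psychiatric disorder (*Power*): 300 × .20 + 450 × .30 = 60 + 135 = 195 events in 750.

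**3. Chance that at least one noise variable enters.** For k independent candidates at entry level .05 this is 1 − .95^k. The P<0.25 screen does not prevent it, because a variable with P<.05 has already passed.
- k = 8: 0.34
- k = 14: 0.51
- k = 20: 0.64

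**4. Simulation of the written procedure.** Settings: 300 replicates per scenario, independent pure-noise predictors, screen at P<.25, forward entry at P<.05, backward removal at P>.10, AUC on the fitting data. The candidate counts and the entry and removal levels are assumptions. The true AUC is 0.50 throughout.

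| Endpoint | Candidates | Forced noise controls | Any selected | Mean AUC if selected | Mean AUC, all runs |
|---|---|---|---|---|---|
| Late relapse, 27 in 325 | 8 | 0 | 38% | 0.641 | 0.553 |
| Late relapse, 27 in 325 | 8 | 6 | 35% | 0.694 | 0.653 |
| Late relapse, 27 in 325 | 20 | 0 | 62% | 0.659 | 0.599 |
| Late relapse, 27 in 325 | 20 | 6 | 71% | 0.715 | 0.690 |
| Psychiatric, 195 in 750 | 20 | 0 | 66% | 0.569 | 0.545 |
| Psychiatric, 195 in 750 | 20 | 6 | 67% | 0.588 | 0.578 |

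With a looser entry level of .15 and 20 candidates, a late-relapse model was selected in 95-96% of runs, with a mean AUC of 0.69-0.73 when selected.

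**The case against.** The strongest reply is that the point rests partly on silence. The protocol does not say that the AUC will be left uncorrected. It introduces its steps as examples, defers to a textbook, expects the models to be refined with co-investigators, and may have a separate analysis plan that adds validation. It also uses the AUC as a measure of fit, not as a claim about new patients. This stands in part: use of the same sample is inferred from the absence of any other data or resampling step. But the protocol does fix the development and assessment rule for every logistic model, and that rule as written gives an optimistic AUC.

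Several stronger readings are tempting and are not supported:
- **That noise alone will usually produce a risk model.** This depends on the number of candidates and the entry level, neither of which is stated. At entry .05 it needs about 14 independent candidates. With about 8, roughly what Hypothesis 4 names, it is 35-38%.
- **That no result could show the model predicts nothing.** Selection can return no predictors. It did so in 29-38% of the late-relapse runs with 20 candidates.
- **That a late-relapse risk tool is a firm aim.** The Background section on late relapse only hedges that identifying people at heightened risk may be possible. Its six items are rival models to contrast, not a stated stepwise pool.
- **That all late-relapse analyses are affected.** Hypothesis 4 also models latency, where the logistic AUC does not arise.

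It is also fair to say that AUCs conditional on selection look worse than averages over all runs, and that a global null is an extreme case. The table therefore shows both averages. The simulation does not reproduce the protocol's ordered entry of predictor groups.

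**Conclusion.** The concern holds in limited form. The AUC from the procedure as written will be optimistic. The optimism is modest for the psychiatric endpoint (about 0.57-0.59 under pure noise) and large for binary late relapse (about 0.66, or about 0.72 with six forced control terms). At about 28 events, a reported late-relapse AUC near 0.70 could not be told apart from noise.

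These sizes rest on an assumed 20 candidates, entry at P<.05, independent predictors and no true effect. Correlated candidates would lower the chance of selection somewhat, and several codings per construct would raise it. The comparison across endpoints is with the psychiatric outcome, the only other binary endpoint with stated rates. The protocol's power figures are not affected.

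**What to change.** Keep the selection procedure and change how its product is assessed and labelled.

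1. In *Predicting Discrete Endpoints*, replace the same-sample AUC with a bootstrap optimism-corrected AUC and a calibration slope. Repeat the P<0.25 screen and the forward and backward steps in every resample. State the entry and removal levels so that they can be repeated.
2. Either fix the best measure of each class beforehand, or give the choice an algorithmic rule so that it can go inside the bootstrap.
3. For Hypothesis 4, base the confirmatory late-relapse model on the predictors that the hypothesis names, and label any wider selected model exploratory.

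A joint likelihood-ratio test of the full candidate set, used as a gate, is not recommended. Simulated with 27 events in 325, six control terms and pure noise (1,500 replicates), the nominal 5% test rejected in about 7%, 10% and 14-15% of runs with 12, 20 and 30 candidates. It could also block the predictors that Hypothesis 4 names.

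The cost is protocol wording and computing time, with no new data or visits. The downside is lower reported AUCs and fewer predictors named.
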